#### Trial management

The trial is registered at clinicaltrials.gov (NCT03870386). The McGill University Health Centre (MUHC) is the coordinating center. An experienced trial coordinator (MM) and the principal investigator (YC) will oversee the proposed RCT. Responsibilities will include overseeing all sites’ ethics submissions, REDCAP-based data collection (monitored every 2 weeks), as well as data clean-up, Good Clinical Practice (GCP) adherence, and staff training. MM will also track all sites’ patient accrual, maintain weekly communication with all sites and issue a monthly newsletter on the trial progress. Each study site will require a trained GCP-certified research assistant to ensure timely accrual and complete data collection. The responsibilities of the research assistants include study start-up review study documents, local adaptation of consent form, training, contract, enrolment, data entry, query resolution as well as extra annual administration tasks submissions for continuing REB review, updating investigator site file and essential documents, as well as AE/SAE reporting.

Scheduled site visits will be performed by the primary investigator (YC) and/or the senior trial coordinator (MM). These scheduled audits will occur at each site between 3 and 6 months post-enrolment commencement. Audited activities include informed consent process, inclusion/exclusion criteria documentation, PI and clinical staff responsibilities and qualifications, protocol deviation management, severe adverse event management, and study documentation process.

### Adverse event reporting

#### Definition of adverse event (AE)

An adverse event is the development of an undesirable medical condition or the deterioration of a pre-existing medical condition following or during exposure to a procedure done, whether or not considered causally related to the procedure. An undesirable medical condition can be symptoms (e.g., nausea, chest pain), signs (e.g., tachycardia, enlarged liver), or the abnormal results of an investigation (e.g., laboratory findings, electrocardiogram).

### Definition of Serious Adverse Event (SAE)

A serious adverse event is an AE occurring during the procedure or any time after the procedure, that fulfills one or more of the following criteria:
Results in deathIs immediately life-threateningRequires in-patient hospitalization or prolongation of existing hospitalizationResults in persistent or significant disability or incapacityIs a congenital abnormality or birth defectIs an important medical event that may jeopardize the patient or may require medical intervention to prevent one of the outcomes listed above

#### Coordinating Center

The Coordinating Center is the central location for the collection and maintenance of documentation of adverse events and is responsible for submitting adverse event reports to the REB promptly. The Coordinating Center will maintain documentation of all adverse event reports for each participating site. Adverse event reports submitted to the Coordinating Center must be signed and dated by the participating site’s Principal Investigator. The Coordinating Center will provide appropriate forms to be used by all participating sites for reporting adverse events. Information to be provided must include:
Subject ID number, and initialsDate of the eventDescription of the eventDescription of site’s response to the eventAssessment of the subject’s conditionSubject’s status on the study (on study, off study, etc.)

#### Participating sites

Participating sites are responsible for reporting adverse events to their REB according to its specific requirements and to the Coordinating Center as follows: Fatal events whether anticipated or unanticipated, and whether or not related to the study, must be reported to the Coordinating Center within 24 h of the participating site Principal Investigator’s learning of the event. Serious and Unanticipated Adverse Events must be reported to the Coordinating Center within 24 h of the participating site Principal Investigator’s learning of the event. Other Serious Adverse Events which may result in a change to the protocol, informed consent, or risk to subjects as specified in the protocol must be reported within three [3] working days of the participating site Principal Investigator’s learning of the event. Adverse events which result in no change to protocol, informed consent, or risk to subjects must be reported to the Coordinating Center on a monthly basis.

All SAEs must be collected whether or not they are considered causally related to the investigational procedure. Investigators and other site personnel are responsible for reporting all casually related SAEs to their REB and the coordinating center.

#### Data Safety Monitoring Board (DSMB)

An independent group of methodologists and physicians will oversee this study DSMB. No member of the DSMB has direct involvement in the conduct of this study or has financial or professional interests that may bias their independent decision making. This committee will meet at the beginning of the trial and will then review possible adverse events on a 6-month basis. Each reviewer will be blinded to the treatment allocation.

During the initial meeting, the committee will discuss the protocol, establish triggers set for data review, and guidelines for monitoring the study. Subsequent meetings will be divided into an open session and closed session. The open session will include the principal investigator, statistician, and all members of the DSMB. The accumulated adverse events, demographic characteristics of enrollees in aggregate, protocol compliance, quality control, and timeliness and completeness of follow-up will be presented by the investigators to the DSMB. The closed sessions will include only members of the DSMB. During this session, members will review the accumulated safety data. The biostatistician for the trial will be available for any questions during this session. Finally, the meeting will conclude with a vote to continue the study, to modify the study, or to terminate the study. A written report by the DSMB will be sent to the principal investigator and REB.

Trial results will be made public through abstract presentation at international gastroenterology conferences including Digestive Disease Week and United European Gastroenterology Week. We will plan to disseminate the results through a full publication in a peer-reviewed medical journal.

## Discussion

The ELEMENT trial is a multi-center randomized trial designed to address the question of whether EUS-BD with LAMS is associated with fewer episodes of stent dysfunction and need for re-intervention compared to standard ERCP in the management of malignant distal biliary obstruction. This clinical trial will also compare the technical and clinical success, adverse events, time to stent dysfunction, and oncological outcomes such as interruptions in chemotherapy, rate of surgical attempt, and survival.

We recently completed a meta-analysis of randomized controlled trials (RCT) comparing EUS-BD vs. ERCP or EUS-BD vs. radiological percutaneous biliary tube drain insertion (PTBD) [14]. Overall, we identified three trials comparing EUS-BD to ERCP [6–8]. Technical and clinical success was similar between modalities; however, rates of re-intervention favored EUS-BD over ERCP (RR 0.40; 95% CI 0.29–094) and PTBD (RR 0.49; 95% CI, 0.28–0.88). In addition, EUS-BD was comparable in terms of safety to ERCP while demonstrating lower rates of adverse events when compared to PTBD (RR 0.59; 95% CI, 0.39–0.87). Although results from this meta-analysis are promising, the studies were single-centered and small, using mostly non-EUS dedicated devices.

The potential for less stent dysfunction requiring reintervention with EUS-BD over ERCP, if shown in our proposed trial, would be of great clinical significance not only because of the diminished morbidity in this often-frail patient population, but also because of the potential impact on oncological outcomes. For patients with metastatic pancreatic cancer with a good performance status, there is a clear survival benefit attributable to FOLFIRINOX therapy [15], which would be necessarily delayed if reinterventions are needed. Furthermore, there has been a push to give neoadjuvant chemotherapy [16, 17] even in resectable disease, meaning that the insertion of a reliable biliary stent that remains patent for longer is likely to become a cornerstone for optimizing oncological outcomes. From a practical efficiency (and perhaps cost-effectiveness) perspective, EUS also has the unique ability to achieve decompression and acquire precise tissue diagnosis at the same clinical setting.

Our trial will be the first multi-center RCT in North America involving the use of a EUS-CDS using a biliary LAMS. The LAMS unique design with bi-flared flanges and short stent length is ideal for apposing two luminal structures for drainage with minimal risk for stent migration. These stents are also cautery-assisted and therefore can be inserted without needing an initial needle puncture and wire insertion, while avoiding the complexity, failure potential, and risks associated with tract dilation and instrument exchange. Retrospective series [10–12] have shown promising results with the largest study demonstrating a technical and clinical success rate of greater than 90%, a low rate of adverse events of 7% with only 9.3% of patients needing re-intervention due to stent dysfunction [12]. Prospective randomized data, however, are lacking and needed. Our multicenter design will not only more definitively provide an adequately powered RCT looking at EUS-BD using a biliary LAMS, but will also produce data generalizable outside the very expert centers.

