**Methods:**

The ELEMENT trial is a multicenter single-blinded RCT involving 130 patients in nine Canadian centers. Patients with unresectable, locally advanced, or borderline resectable malignant distal biliary obstruction meeting the inclusion and exclusion criteria will be randomized to EUS-choledochoduodenostomy using a LAMS or ERCP with traditional metal stent insertion in a 1:1 proportion in blocks of four. Patients with hilar obstruction, resectable cancer, or benign disease are excluded. The primary endpoint is the rate of stent dysfunction needing re-intervention. Secondary outcomes include technical and clinical success, interruptions in chemotherapy, rate of surgical resection, time to stent dysfunction, and adverse events.

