### Randomization

Patients included are randomized in a 1:1 ratio, in blocks of four, stratified by site and resectability: borderline resectable/locally advanced versus unresectable malignant distal biliary obstruction (Fig. 2 via secure Internet software (randomize.net)). Patients are randomized by a research assistant following consent. The endoscopist is then informed of the treatment allocation and the research nurse will verify that the correct assigned procedure is carried through and documented.

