### Analyses

An intention-to-treat analysis along with a secondary per-protocol analysis will be carried out. Descriptive statistics will assess the adequacy of patient characteristics and balancing of the randomization process. Inferential analysis will employ Student’s *t* test and Chi-square testing. Survival analysis using the Kaplan–Meier method will be used to assess stent patency time. A step-wise multivariate regression analysis will be undertaken to identify independent predictors of stent dysfunction and adverse events using a log-rank test. A *p* value of 0.05 or less will be considered statistically significant. All analyses will be performed using SAS version 9.4. No interim analysis is planned given the short accrual time, relative small sample size, and short follow-up period.

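### The stated analysis of the surgical outcome ignores the resectability stratum, which shrinks the absolute difference and costs some power; a low-priority improvement

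*Protocol article*

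**What the plan says.** Surgery appears twice as an outcome to be compared. The abstract (Methods) states: "Secondary outcomes include technical and clinical success, interruptions in chemotherapy, rate of surgical resection". The Discussion says the trial will compare "oncological outcomes such as interruptions in chemotherapy, rate of surgical attempt, and survival". Neither place gives a denominator, and surgery is in neither the secondary nor the additional list of Table 3.

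The Analyses section gives one rule for all endpoints: "An intention-to-treat analysis along with a secondary per-protocol analysis will be carried out", with Student's t test and chi-square for inference. No stratified test is named, and no endpoint is limited to part of the trial.

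The Randomization section says allocation is "stratified by site and resectability: borderline resectable/locally advanced versus unresectable malignant distal biliary obstruction". Unresectable patients are eligible under Table 1. Patients with clearly resectable disease are not: "Patients with hilar obstruction, resectable cancer, or benign disease are excluded".

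**The concern.** The Discussion argues that a stent that stays patent longer could improve oncological outcomes, and it refers to neoadjuvant treatment. For surgery, that question mainly concerns patients who might still come to an operation. Patients classed as unresectable at entry probably add few events to the numerator, but they count in full in both denominators.

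The absolute difference then depends partly on case mix, and an unstratified test sets aside a factor that the design already balances. Because the stratum is fixed before allocation, a comparison by allocated arm within it, or stratified by it, is still a randomised, intention-to-treat comparison. What is at stake is how the surgical result is read, and some of its power. The primary analysis is untouched.

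**Working it through.** **Reproducing the plan's own figure.** No sample size is given for surgery, so the method is checked on the primary endpoint (30% v 10%, two-sided 5%, 80% power):

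n per arm = [1.960·√(2·0.20·0.80) + 0.842·√(0.30·0.70 + 0.10·0.90)]² / 0.20² = (1.109 + 0.461)² / 0.04 = 61.6, so 62 per arm and 124 in total. This agrees with the sample size section.

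**Inputs for surgery.** From the article: 65 per arm, two-sided 5%, chi-square. Assumed, because the article does not give them: an unresectable share of 30%, 50% or 70% (46, 32 or 20 per arm in the other stratum); no surgery in the unresectable stratum; and the surgery rates in the table.

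**Effect size.** Let f be the share in the borderline resectable/locally advanced stratum, and p1, p2 the surgery rates there.
- All-patient difference = f·p2 − f·p1 = f·(p2 − p1), so it shrinks by the factor f.
- All-patient ratio = f·p2 / (f·p1) = p2/p1, so it is unchanged.
- Example with half unresectable and 60% v 30%: 19.2 v 9.6 expected events. Over 32 per arm the difference is 30 points; over 65 per arm it is 29.5% v 14.8%, about 15 points. The ratio is 2.0 in both.

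**Test statistic.** With p the mean rate in the stratum, the all-patient z divided by the stratum z is √((1 − p)/(1 − f·p)). In the example, f = 32/65 = 0.492 and p = 0.45, which gives √(0.55/0.778) = 0.84. The loss is smaller than the shrinkage of the difference, because patients without events also add little variance. It fades when surgery is rare.

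**Power.** Exact binomial power of the uncorrected chi-square, all patients v stratum only, in percent:

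| Surgery in stratum | 30% unresectable | 50% unresectable | 70% unresectable |
|---|---|---|---|
| 60% v 30% | 78 v 83 | 54 v 71 | 28 v 46 |
| 70% v 40% | 75 v 83 | 48 v 71 | 22 v 46 |
| 50% v 30% | 44 v 49 | 26 v 39 | 14 v 24 |
| 60% v 40% | 39 v 48 | 21 v 39 | 9 v 22 |
| 40% v 20% | 51 v 56 | 33 v 42 | 20 v 29 |
| 30% v 15% | 37 v 41 | 25 v 30 | 15 v 20 |
| 25% v 10% | 45 v 49 | 32 v 36 | 18 v 24 |
| 20% v 10% | 25 v 28 | 18 v 21 | 11 v 14 |

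Before rounding, the gain is 2.8 to 5.3 points in the last three rows, 5 to 18 points for 20-point differences, and 5 to 25 points for 30-point differences. The method of calculation matters too: for 50% v 30% with half unresectable, a normal approximation gives 30% v 37% instead of 26% v 39%.

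**A stratified test that keeps everyone.** With no events in the unresectable stratum, that stratum adds nothing to the Cochran-Mantel-Haenszel numerator or variance. The test over all randomised patients then has the stratum-only power (71% in the 60% v 30%, half-unresectable case). If 2% of unresectable patients also have surgery, simulation of that case (200,000 trials) gives 65% stratified v 53% unstratified.

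**The case against.** The all-patient denominator is inferred. It comes from a general rule in a condensed article, and no sentence applies it to surgery. A full protocol or analysis plan that is not shown may set something else. Intention-to-treat does not rule out a stratified comparison. This stands as a limit: the point concerns the one rule the article states, and it lapses if the analysis plan already stratifies.

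The effect sizes that make the loss look large are generous. The trial assumes a 20-point gap in re-intervention (30% v 10%). If better patency were the only route to more surgery, and every dysfunction cancelled an operation, the surgical difference would be about 20 points, provided that gap holds in the stratum. The 30-point rows lie beyond that. With 10- to 15-point differences the gain is small. This also stands.

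A reader might infer three stronger things that the documents do not support:
- *That unresectable patients cannot have the event.* Table 1 bases resectability on imaging and physician evaluation, surgical attempt is undefined, and follow-up can end at surgery for any patient. Few events is a reasonable expectation; none is an assumption.
- *That the all-patient difference is wrong.* It is a valid, unbiased effect for the population enrolled, and its risk ratio is not diluted when the unresectable rate is zero.
- *That the stratum result should replace it.* The two answer different questions. The retained stratum is itself mixed, since it pools borderline resectable with locally advanced disease.

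**Conclusion.** The point holds in a limited form. The article compares surgery between arms, its only stated analysis is unstratified, and it leaves unused a pre-randomisation stratum that probably determines much of who has the event. The absolute difference shrinks roughly in proportion to the unresectable share. The power loss is about 2 to 6 points in most smaller-effect scenarios and reaches about 24 to 25 points only at the extreme (70% v 40% with 70% unresectable).

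These sizes rest on assumed stratum shares, assumed surgery rates and zero events in the unresectable stratum. Nor would the change make the surgical comparison adequately powered: after stratification, power passes 80% only in the 30-point rows with 30% unresectable. The main gain is a result that can be read for the patients who might reach surgery. It is a low-priority improvement.

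**What to change.** Add one sentence to the Analyses section: the surgical outcome is tested by allocated arm, stratified by resectability at randomisation (for example Cochran-Mantel-Haenszel), in all randomised patients. Report the risk difference with 95% CI within the borderline resectable/locally advanced stratum beside the all-randomised rate in each arm, and give the count of operations in the unresectable stratum descriptively.

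No new data are needed, because the stratum is recorded when the patient is randomised. The cost is one more reported estimate for a minor, unpowered outcome. The same edit is a convenient place to use one term for the event, since the abstract says resection and the Discussion says attempt; that is a separate matter and does not alter the point here.

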## Conclusions

The role of EUS-BD in malignant distal biliary obstruction as a primary modality is a timely question that has not been studied with the performance of a multi-center RCT. The ELEMENT trial aims to ascertain whether EUS-CDS with LAMS is superior to ERCP in malignant distal obstruction adopting the primary endpoint of stent dysfunction. The results will likely impact clinical practice in an era of growing neoadjuvant chemotherapy use, by optimizing stable and reliable sustained biliary drainage.

## Trial status

Recruiting, start date: 03/13/2019.

Approximate date when recruitment will be completed: 03/03/2020.

## Data Availability

The datasets used and/or analyzed during the current study are available from the corresponding author on reasonable request.

## Abbreviations

BD: Biliary drainage
CI: Confidence interval
ERCP: Endoscopic retrograde cholangiopancreatography
EUS: Endoscopic ultrasound
PTBD: Percutaneous transhepatic biliary drainage
RCT: Randomized controlled trial
RR: Risk ratio
